### Research question one

Gait analysis outcome variables and muscle activations will be modelled as the dependent variables, ‘timepoint’ will be the fixed effect of interest, and participants will be defined as a random effect [17].

### Research question two

Pain will be modelled as the dependent variable, ‘timepoint’ will be the fixed effect of interest, and participants will be defined as a random effect.

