Previous research has found an association between prosthetic use and the prevalence of LBP amongst persons with traumatic LLA [35, 36]. As persons with traumatic LLA are generally younger and more active compared to individuals with vascular LLA [26], greater prosthetic use amongst this population may predispose individuals to LBP. Research has proposed that the severity of LBP is greater with more proximal amputation locations [23, 37–39]. However, discrepancies exist within the literature regarding the accuracy of these findings [26]. When studying LBP prevalence amongst persons with LLA, it is important to account for one’s activity levels, time spent active on the prosthesis, the number of years of prosthetic use, and psycho-social factors, such as anxiety and depression [26].

The association between amputation and pain is unclear due to the multifactorial nature of each condition. In addition, variables such as age, pre-existing pain, and clinical characteristics of people with limb loss are rarely taken into account, and with that, small sample sizes typically engaged in this research domain makes inferences greatly limited for specific patient groups. There is evidence that LBP is more bothersome than PLP and RLP [23], and is associated with shorter walking distances one-year post amputation [40, 41]. Risk factors for LBP include type and level of amputation and prosthesis, poor prosthetic fit, gait modifications, limb-length discrepancies, and psycho-social factors such as fear avoidance and depression [42].

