### Objectives and hypotheses

To address this gap, the proposed study protocol will explore the bio-behavioural, psychological, and social characteristics of LBP amongst persons with unilateral LLA over a period of 12-months after their amputation. The whole spectrum of LBP will be explored, including both acute and chronic LBP. To date, this has not been explored in the current literature, and is therefore a novelty and strength of the proposed protocol. Specifically, interactions between bio-behavioural factors of movement (i.e. gait characteristics, trunk and lower-limb muscle activations), and the psycho-social aspects of pain and function will be investigated. Here, the term ‘function’ refers to the comprehensive overview of each participant’s everyday interactions and long-term targets, defined by the participant in terms of person-specific activities and goals. Consideration of these variables aim to improve an understanding grounded in patient-specific function, helping to decipher the relationships between the biopsychosocial characteristics of LBP in individuals with LLA. In doing so, this investigation looks to inform tailored care management and rehabilitation processes.

We hypothesise that individuals who display fear avoidance behaviours will have altered joint range of motion, which in turn will influence muscle activation patterns, leading to greater loading on one side and asymmetries between the sound and residual limb, and therefore increase the risk of LBP development.

Hypothesis 1 (HA1): Gait characteristics will change with time post-amputation and will stabilise following a reduction in movement pattern and trunk muscle activation asymmetries.Hypothesis 2 (HA2): Individuals with a greater risk factor pattern of stressors will experience more pain following the amputation.Hypothesis 3 (HA3): Persons with LLA who experience different types of pain will be at a greater risk of reduced functionality over time.Hypothesis 4 (HA4): Greater scores on psycho-social assessment of pain questionnaires, asymmetric gait patterns, greater and asynchronous activation of trunk muscles, and changes in spatiotemporal characteristics of gait, such as slower gait speed, will be associated with altered pain and function.

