### Statistical analysis

All biomechanical data will be processed in MATLAB® R2023a (MathWorks, Inc) and OpenSim and reported as mean ± standard deviation. Statistical analysis will be conducted using IBM SPSS software (Version 26.0. Armonk, NY). Descriptive data obtained from anthropometrics, online questionnaires, and gait parameters will be analysed by descriptive statistical methods. Biomechanical and psycho-social data will be inputted into a random forest algorithm, which will be used as a dimensionality reduction approach to better explain the variance of the LBP data distribution [72]. Thus, this approach will allow us to evaluate how important each factor is influencing the final outcome (i.e. LBP presence). The process of feature selection is a type of exploratory analysis based on the Pearson’s *r* correlation coefficient to estimate correlations between all the variables collected and LBP. The application of random forest analysis in clinical research is considered a key step towards improving patient related health outcomes [73]. Clinical studies in the literature support the use of random forest analysis for classification performance and prediction, for example in the diagnosis of breast cancer using mammography imaging techniques [74]. Generalised linear mixed models will be used to examine the contributions from biomechanical and psycho-social variables to predict the development of LBP. The variables included in the analysis will be selected based on previous studies [17, 26, 47] and the results from the random forest analysis. Generalised linear mixed models will then be created to identify the best predictors to answer research questions two, three, and four, with pain as a ‘yes/no’ binary variable, and a linear mixed effects model will investigate research question one. Significance will be accepted at *p* < 0.05.

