#### Research question three

Function will be modelled as the dependent variable, ‘timepoint’ and pain will be the fixed effects of interest, and participants will be defined as a random effect.

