#### Research question four

Pain and function will be modelled as the dependent variable, ‘timepoint’, biomechanical, and psycho-social variables will be the fixed effects of interest, and participants will be defined as a random effect.

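### As written, the research question two model tests whether pain changes over time, not hypothesis 2, and it conflicts with the statement that predictors will be identified for it

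*Protocol article*

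**What the plan says.** Four parts of the protocol article bear on this.

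- **Objectives and hypotheses**, hypothesis 2: "Individuals with a greater risk factor pattern of stressors will experience more pain following the amputation".
- **Research question two**, the model: "Pain will be modelled as the dependent variable, ‘timepoint’ will be the fixed effect of interest". Participants are the random effect. No other term is named.
- **Research questions three and four**, for comparison. Question three, with function as outcome, has "timepoint’ and pain will be the fixed effects of interest". Question four, with pain and function as outcomes, has "timepoint’, biomechanical, and psycho-social variables will be the fixed effects of interest".
- **Statistical analysis**, general paragraph: "Generalised linear mixed models will then be created to identify the best predictors to answer research questions two, three, and four", and this is to be done "with pain as a ‘yes/no’ binary variable". Candidate variables are to come from previous studies and from a random forest.

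Study outcomes gives five visits over 12 months. Table 2 there lists the variables measured, among them fear of movement, anxiety and depression, limb-length discrepancy, socket comfort and pain intensity.

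**The concern.** Hypothesis 2 concerns differences between people, while the model attached to it describes differences between visits. If the model is run as its own section states, the reported p-value answers whether average pain moved over the year. A significant time effect could be read as support for hypothesis 2, and a null one as evidence against it. It would be neither.

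The general paragraph does not settle the matter. An analyst who follows it would bring predictors in after a random forest and correlation screen against low back pain in the same 30 or so people. An analyst who follows the section on research question two would bring in none. The two would report different analyses under the same label, and in neither case has the risk-factor pattern, or the coefficient that tests it, been fixed in advance.

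**Working it through.** **1. No figure in the plan is tied to this hypothesis.** The Sample size section says its calculation covers kinematic variables only. For completeness, its N = 26 (effect size 1.03, α = 0.05, power 0.80) reproduces as a one-sided two-group t-test with 13 per group and power 0.818. Nothing below depends on it.

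**2. Terms of the model against the hypothesis.** For person i at visit j, with binary pain and a participant intercept, the section on research question two gives

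logit P(pain_ij) = β0 + β_j + u_i, with u_i ~ N(0, σ²).

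With five visits as a factor, the parameters are one intercept, 5 − 1 = 4 time contrasts and one variance. Hypothesis 2 needs a person-level risk score S_i:

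logit P(pain_ij) = β0 + β_j + γ·S_i + u_i, with γ > 0 as the claim.

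γ is not in the written model. Any true difference between high-risk and low-risk people is absorbed into u_i.

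**3. Is the omission only shorthand?** Set side by side:

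| Research question | Outcome | Fixed effects named |
|---|---|---|
| One | Gait and muscle activation | Timepoint |
| Two | Pain | Timepoint |
| Three | Function | Timepoint, pain |
| Four | Pain and function | Timepoint, biomechanical, psycho-social |

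Questions three and four name their explanatory variables. Question one needs none beyond time, because hypothesis 1 is about change over time. Question two alone lacks the variable its hypothesis is about.

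**4. Illustration.** These assumptions are not in the documents: 27 completers (30 × 0.9), five visits, 60% chance of pain for a person of average risk, no true time trend, a standard normal risk score, random-intercept SD of 1 or 2, and 400 runs per cell. The time-only test was a marginal logistic (GEE) Wald test of timepoint. The risk test was a simple correlation of the score with each person's proportion of visits with pain. Percentages of runs rejecting at 0.05, for intercept SD 1 / SD 2:

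| Odds ratio per SD of risk | Timepoint test | Risk-score test |
|---|---|---|
| 1 | 5.25 / 3.5 | 6.75 / 5.5 |
| 2 | 3.0 / 2.25 | 63.5 / 28.5 |
| 3 | 3.25 / 3.0 | 94 / 57 |
| 5 | 4.25 / 2.25 | 99.5 / 82.5 |

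The timepoint test stays near or below its nominal level whatever the strength of the risk effect. The risk-score test responds to it, though with limited power for moderate effects when people vary a good deal.

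**5. Outcome scale.** Hypothesis 2 speaks of more pain, while the general paragraph makes pain binary. Even with γ added, the test would concern presence of pain, not its amount.

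**The case against.** The best defence is that the section on research question two should not be read alone. It calls timepoint the effect of interest, which is not the same as the only fixed effect. The general paragraph says mixed models will "identify the best predictors to answer research questions two, three, and four". Research question four will in any case estimate psycho-social and biomechanical associations with pain. The study is exploratory, and the article admits that it is not powered for the psycho-social variables.

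Much of this stands. A reader might infer that the plan as a whole holds no information on hypothesis 2, and the documents do not support that: question four will produce relevant coefficients, and the general paragraph shows an intention to use predictors for question two. But that intention contradicts the model as specified and does not complete it. Question four goes with hypothesis 4, and it neither defines a risk-factor pattern nor names a contrast for hypothesis 2.

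The link between question two and hypothesis 2 is also inferred from matching numbers, since the article has no separate list of research questions. The other three pairs match in content. If the second pair does not, hypothesis 2 has no assigned analysis at all.

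A reader might also infer that leaving amputation level out of the models confounds the gait–pain association in question four, since the introduction says "Risk factors for LBP include type and level of amputation and prosthesis, poor prosthetic fit, gait modifications, limb-length discrepancies". The documents do not establish this. The same section describes the evidence on level as inconsistent. Table 2 covers biomechanical and psycho-social variables treated as dependent variables, so a fixed baseline characteristic need not appear there. The general paragraph also lets covariates enter from previous studies.

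**Conclusion.** The concern holds as a mismatch between the hypothesis, the general analysis paragraph and the model for research question two. The stated test for that question is of change in pain over time, and no coefficient in the model bears on hypothesis 2. One of four hypotheses therefore lacks a working prespecified test, although related associations will be estimated under question four.

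The conclusion rests on two readings: that question two is meant to test hypothesis 2, and that the question-specific section sets out the model's fixed effects. The structural argument needs no numerical assumption; the simulation only illustrates it. Amputation level is at most an optional covariate and is not part of this finding.

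**What to change.** Reconcile the Statistical analysis paragraph with the section on research question two, as follows.

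- Add a risk-factor term to the model and keep timepoint and the participant random effect. Define the term before outcomes are examined, from visit-1 values of variables already in Table 2, for example fear of movement, anxiety and depression, socket comfort and limb-length discrepancy. State how the items are combined.
- Declare the coefficient of that term to be the test of hypothesis 2. Report the timepoint effect as a description of the course of pain.
- Pain at visit 1 is measured at the same time as a visit-1 score. Either take pain at visits 2 to 5 as the outcome or state that the association is partly cross-sectional.
- Say whether hypothesis 2 concerns presence of pain, in which case the binary outcome fits, or amount, in which case use the pain intensity already collected.

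No new data are needed. A single score costs one degree of freedom, and separate items cost one or more each, in about 30 people. The simulated power figures used all five visits, so using visits 2 to 5 would be expected to give somewhat less. Report the result as exploratory, with the estimate and its confidence interval.

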#### Research question three

Function will be modelled as the dependent variable, ‘timepoint’ and pain will be the fixed effects of interest, and participants will be defined as a random effect.

#### Research question four

Pain and function will be modelled as the dependent variable, ‘timepoint’, biomechanical, and psycho-social variables will be the fixed effects of interest, and participants will be defined as a random effect.

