## Methods and analysis

### Study design

This research is a prospective longitudinal study that aims to explore the potential mechanistic pathways of LBP development amongst persons with unilateral LLA. The dataset will include data collection every 3-months over a 12-month period (Fig 1). All testing procedures will take place at the local rehabilitation centre where patients are currently registered for their post-amputation rehabilitation (either the Bristol Centre for Enablement, North Bristol NHS Trust or the Portsmouth Enablement Centre, Portsmouth Hospitals University NHS Trust). Measurement sessions will occur following patients’ routine visits to the centres, ensuring that the testing sessions are structured around the patient’s availability to improve study recruitment and retention. Biomechanical gait variables and muscle activations of trunk and sound lower-limb muscles will be monitored, and objective measurements of different sources of pain and physical activity will be determined using online questionnaires.

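### The overarching hypothesis is a mediated chain from fear avoidance to lower back pain, but no stated model relates fear to gait or muscle activation, and question four's fear coefficient can be only a direct effect

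*Protocol article*

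**What the plan says.** Under Objectives and hypotheses, the protocol article sets out one ordered hypothesis. Its first steps read: "We hypothesise that individuals who display fear avoidance behaviours will have altered joint range of motion, which in turn will influence muscle activation patterns". The same sentence then gives the remaining steps, from muscle activation to pain, as: "leading to greater loading on one side and asymmetries between the sound and residual limb, and therefore increase the risk of LBP development". Study design says that the research "aims to explore the potential mechanistic pathways of LBP development amongst persons with unilateral LLA". Objectives and hypotheses also promises to investigate "interactions between bio-behavioural factors of movement" together with the psycho-social side of pain and function. The numbered hypothesis HA4 is weaker: psycho-social scores, gait asymmetry, trunk activation and spatiotemporal change are expected to be associated with pain and function.

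The sections on the four research questions name these models, each with participant as a random effect:

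| Question | Outcome | Fixed effects named |
|---|---|---|
| 1 | gait and EMG | timepoint |
| 2 | pain | timepoint |
| 3 | function | timepoint, pain |
| 4 | pain and function | timepoint, biomechanical, psycho-social |

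For question one, "Gait analysis outcome variables and muscle activations will be modelled as the dependent variables". For question four, "biomechanical, and psycho-social variables will be the fixed effects of interest". Table 2 lists fear of movement as psycho-social, and joint angles, muscle activations and asymmetries as bio-behavioural. Statistical analysis adds a random forest and Pearson correlations of the collected variables with LBP. These feed the choice of predictors for questions two to four; question one gets a linear mixed model.

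**The concern.** The hypothesis makes a claim about each step, beginning with fear altering movement. A reader would expect at least one model with movement as the outcome and fear as a predictor. Gait and EMG are outcomes only in question one, where timepoint is the only predictor named.

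Fear can meet the movement variables in question four, but as a fellow predictor of pain. There its coefficient describes the association with pain that does not run through the movement variables in the same model. The chain, read literally, predicts no such remainder. A null fear coefficient could then be taken to mean that fear does not matter, and joint significance could be taken as support for the chain. Neither inference would follow. Fear is a candidate target for the tailored care that the study hopes to inform, so its role should not rest on a coefficient that answers another question.

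**Working it through.** **Step 1: links against models.** The chain has four links: fear to range of motion (ROM), ROM to EMG, EMG to asymmetry, and asymmetry to LBP. The first three need a movement variable as outcome and its upstream variable as predictor, and no stated model has that form. The fourth can be read from RQ4. The random forest and correlation step relates variables to LBP, not fear to gait.

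**Step 2: what the chain predicts.** Take standardised variables with path *p* per link: ROM = *p*·fear + e1, EMG = *p*·ROM + e2, asymmetry = *p*·EMG + e3, and log-odds of LBP = *b*·asymmetry + participant effect.
- Fear's effect on asymmetry is *p*³: 0.6³ = 0.216 and 0.8³ = 0.512.
- With *b* = 1.5, fear's total effect on the log-odds is *b*·*p*³: 1.5 × 0.216 = 0.324 and 1.5 × 0.512 = 0.768, before the attenuation that comes from averaging over the other variation.
- Given ROM, EMG and asymmetry, fear's effect is 0 for any *p* and *b*.

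**Step 3: simulation inputs.** The article gives no figure for this point; its N = 26 rests on kinematic variables alone (Sample size). From the article: 30 participants and 10% dropout, so 30 × 0.90 = 27 completers; 5 visits; significance at 0.05. Assumed: the paths, intraclass correlation 0.5, asymmetry log-odds 1.5 per SD and participant SD 0.7. The model was a logistic GEE with exchangeable correlation, standing in for the mixed model, with 400 runs. The cells show fear's log-odds ratio for LBP and the share of runs with fear significant.

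| Scenario | Without intermediates | With intermediates | Asymmetry on fear, significant |
|---|---|---|---|
| Full chain, *p* = 0.8 | 0.60 (83%) | -0.01 (8%) | 100% |
| Full chain, *p* = 0.6 | 0.23 (23%) | 0.00 (8%) | 76% |
| Short chain: fear to asymmetry 0.7 | 0.85 (96%) | 0.02 (9%) | 100% |
| Full chain, *p* = 0.8, intermediates' reliability 0.7 | 0.59 (80%) | 0.09 (10%) | 99.5% |
| Short chain, reliability 0.7 | 0.86 (98%) | 0.48 (44%) | 100% |
| Fear and gait unrelated, each acting on LBP (log-odds 1.0) | 0.74 (91%) | 1.00 (96%) | 7% |

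With 2,000 participants (15 runs) and well-measured intermediates, the joint coefficient under the three true chains stayed between -0.01 and 0.01. The near-zero value is therefore not a small-sample effect. In the last row, fear and at least one gait variable were both significant in 96% of joint-model runs.

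**Step 4: weaker assumptions.** A second simulation used 30 participants, a random-intercept logistic model, asymmetry log-odds 1.0, participant SD 1 and 300 runs.

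| Path per link | 0.4 | 0.5 | 0.6 | 0.7 | 0.8 |
|---|---|---|---|---|---|
| Fear significant, without intermediates | 6% | 7% | 12% | 30% | 51% |
| Fear significant, with intermediates | 4.7% | 5.0% | 6.7% | 7.7% | 7.3% |
| All four links significant | 85% | 95% | 94% | 85% | 80% |

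The Monte Carlo standard error near 6% is √(0.06 × 0.94 / 300) = 1.4 percentage points, so the first two rows cannot be told apart at paths of 0.4 and 0.5. At path 0.8 with log-odds 1.5, the figures were 83% without and 4.3% with the intermediates.

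**The case against.** Much of the opposing case stands.

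- **RQ4 fits HA4.** HA4 claims association, and RQ4 uses its outcomes and predictor groups. Nothing says that RQ4 tests the chain. The mismatch is with the overarching hypothesis and the mechanistic aim, not with HA4.
- **Fear's unadjusted association would be seen.** The planned correlations with LBP include it, so fear need not vanish from the results.
- **Model content is not settled.** Variables are selected before modelling, and selected predictors may also enter questions two and three. Fear and its intermediates may or may not share a model. But extra predictors there would still leave pain or function as the outcome, so the movement links stay unmodelled.
- **Masking is conditional.** A direct path or measurement error leaves part of fear's effect visible (44% in the short chain at reliability 0.7). With paths of 0.4 to 0.6 in the second simulation, fear was rarely detected even without the intermediates (6-12%).
- **An unseen analysis plan could add mediation.** It could. The point rests on the models that the article itself assigns to its questions.

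A reader might go further and infer that a true chain makes fear look irrelevant, that a broken chain will look supported, and that RQ4 should be replaced. The documents do not support this. The first needs near-full mediation and well-measured intermediates, and the article gives no path values. The second assumes that joint significance would be read as evidence for the chain, which no section says; in the simulated case both effects were real, and RQ4 reported them correctly. The third would discard the model that suits HA4.

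**Conclusion.** The point holds in a limited form. The overarching hypothesis is a mediated chain, and no stated model relates fear to gait or EMG, so the first three links go untested. Where fear and its intermediates enter RQ4 together, the fear coefficient is a direct effect and not a test of the chain or of fear's overall role.

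That the direct effect is zero under full mediation follows from the algebra. How much this masks fear depends on assumptions. With well-measured intermediates and asymmetry log-odds of 1.5, detection is 8-9% with the intermediates against 23-96% without them. With weak paths the difference all but disappears. What separates a true chain from a broken one in the first simulation is the model of asymmetry on fear: significant in 76-100% of runs when the chain is true and 7% when fear and gait are unrelated.

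**What to change.** - Keep RQ4 as the analysis for HA4.
- Add mixed models with ROM, EMG and asymmetry in turn as outcome and the upstream variable as predictor, beginning with fear of movement. Preferably take the predictor from the earlier visit, because same-visit regressions say nothing about order. Five visits give four lagged pairs per participant, at most 27 × 4 = 108 among 27 completers.
- Report fear's association with LBP both with and without the gait, EMG and asymmetry terms.
- State that the fear coefficient in RQ4 is a direct effect only where those terms are in the model, and that joint significance there is not evidence for the chain.
- Label the chain analysis exploratory. Link and indirect estimates from about 27 completers will be imprecise and remain observational, and Sample size already concedes that the psycho-social analyses are not powered.

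The cost is added wording and a few extra models on data already being collected, with no further patients or measurements. The price is a more cautious mechanistic claim.

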### Study population

The recruitment of 30 NHS patients, over 18 years old, with unilateral TFA and TTA will be attempted from the Bristol Centre for Enablement and the Portsmouth Enablement Centre. These centres host a large heterogeneity of patients, allowing us to recruit individuals with different levels of amputation (above/below the knee) and cause of amputation (traumatic/vascular/cancer causes). Furthermore, the rehabilitation programme provided to patients across these centres are very similar regarding aims and outcomes, and the present study will run in parallel with the patients’ personal goals.

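### RQ4 enters visit-varying predictors unsplit, so each coefficient blends within-person change with between-patient differences that stable traits can confound

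*Protocol article*

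**What the plan says.** The protocol article, Research question four, models pain and function with timepoint as a fixed effect and adds: "biomechanical, and psycho-social variables will be the fixed effects of interest, and participants will be defined as a random effect". Research question three has the same structure, with pain as a fixed effect for function. Neither section separates a person's average level from visit-to-visit change.

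Statistical analysis gives the purpose: "Generalised linear mixed models will be used to examine the contributions from biomechanical and psycho-social variables to predict the development of LBP". It describes how terms are chosen: "The variables included in the analysis will be selected based on previous studies [17, 26, 47] and the results from the random forest analysis". The feature screen is "based on the Pearson’s *r* correlation coefficient to estimate correlations between all the variables collected and LBP".

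The background section on low back pain (LBP) characteristics and gait says of earlier work that "variables such as age, pre-existing pain, and clinical characteristics of people with limb loss are rarely taken into account". It also says that "it is important to account for one’s activity levels, time spent active on the prosthesis, the number of years of prosthetic use", together with psycho-social factors, and it lists type and level of amputation among the risk factors for LBP. It contrasts patient types: "As persons with traumatic LLA are generally younger and more active compared to individuals with vascular LLA". Study population presents the mix of amputation levels and causes as an advantage of the two centres. Table 2 lists prosthesis type and anthropometrics under a separate group that research question four does not mention. Age, cause and level of amputation are not in that table.

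**The concern.** A participant random intercept accounts for correlation among one person's five visits. It does not remove confounding by stable traits, because it assumes that the person effect is independent of the predictors. If cause of amputation or age influences both a gait measure and the chance of pain, that assumption fails, and the single coefficient becomes a weighted mixture of a within-person and a confounded between-person association.

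The protocol itself describes such a trait: traumatic and vascular patients differ in age and activity, and the authors suggest that greater prosthetic use may predispose the former to LBP. The study design aims at possible mechanistic pathways of LBP development, and the results are meant to inform rehabilitation. At stake is whether a reported predictor means that pain follows a change in gait or fear in the same person, or only that one type of patient differs from another. The stated model cannot tell these apart.

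**Working it through.** **Plan figures used.** The protocol gives no operating figure for this model, and its sample size section says that the calculation covers kinematic variables only. Taken from it are 30 recruited and 10% drop-out, so 30 × 0.9 = 27 people, and 5 visits from Study outcomes. Everything else below is assumed.

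**Set-up.** A stable trait Z (SD 1) shifts the log-odds of pain by g per SD and correlates 0.7 with the person-level part of a predictor x (total SD 1, intraclass correlation ICC). The residual random-intercept SD is 1. x has no effect on pain.

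**What the between-person slope should be.** The variance of a person's mean over 5 visits is ICC + (1 − ICC)/5. The slope of the log-odds on that mean is approximately

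b_between = 0.7 · g · √ICC / [ICC + (1 − ICC)/5].

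For ICC 0.5 and g = 1 this is 0.7 × 0.707 / 0.6 = 0.825. The true within-person slope is 0. The unsplit coefficient should lie between the two.

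**Simulation.** Random-intercept logistic model fitted by quadrature, likelihood-ratio tests at 5%, 200 replicates per row:

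| ICC | g | b_between | median unsplit log-odds ratio | unsplit rejects | deviation term rejects | unsplit, trait added, rejects |
|---|---|---|---|---|---|---|
| 0.5 | 1.0 | 0.83 | 0.31 | 21.5% | 3.5% | 5.5% |
| 0.5 | 1.5 | 1.24 | 0.41 | 23% | 1.5% | 4% |
| 0.7 | 1.0 | 0.77 | 0.44 | 34% | 3.5% | 6% |
| 0.7 | 1.5 | 1.16 | 0.59 | 43% | 1.5% | 4.5% |
| 0.85 | 1.0 | 0.73 | 0.57 | 42.5% | 3.5% | 8% |
| 0.85 | 1.5 | 1.10 | 0.77 | 63% | 1.5% | 5.5% |

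The unsplit coefficient lies between 0 and b_between in every row and takes a larger share of it as ICC rises: 0.311/0.825 = 38% at ICC 0.5 and 0.567/0.733 = 77% at ICC 0.85 (g = 1). The spurious odds ratios run from exp(0.31) = 1.36 to exp(0.77) = 2.16 per SD. The Monte Carlo standard error is √(0.215 × 0.785/200) = 2.9 points for the lowest unsplit rate and √(0.05 × 0.95/200) = 1.5 points at the nominal level. The rows share random numbers, so the repeated 3.5% and 1.5% are not independent results.

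**Other assumptions.**
- Logistic model with exchangeable working correlation and robust errors as a stand-in, 600 datasets per scenario, trait correlations 0.5 to 0.7, ICC 0.5 to 0.7: the unsplit term rejects in 12% to 38% (odds ratio about 1.12 to 1.40), the deviation term in 6% to 7%. Without confounding both reject in 6% to 8%.
- A further run with 27 people, 5 visits and other assumed trait strengths: 16% to 49% unsplit, 5% to 7% for the deviation term.

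**Limits and cost of the split.**
- If the trait also alters the slopes of predictor and outcome over time (assumed correlation 0.6, ICC 0.6, 500 replicates), the deviation term rejects in 10% to 15%, against 6% with constant effects.
- With a true effect of 0.5 log-odds per SD, no confounding and ICC 0.6 to 0.7, power is 53% to 58% unsplit and 26% to 30% for the deviation term. A separate run gave 56% to 57% and 25% to 34%.

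**The case against.** **The covariate list is not closed.** Research question four lists effects of interest, and Statistical analysis allows terms from previous studies and from a screen of all collected variables. One of the cited sources is the one that the background relies on for the need to account for activity and prosthetic use. This stands: a reader might infer that the plan excludes age, cause or level of amputation, and the text does not say so. What remains is that none is named or forced in. A marginal correlation with LBP does not select for confounders and can favour a confounded predictor.

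**The hypotheses are largely between-person.** Hypotheses 2 and 4 are worded mainly as comparisons of people with higher and lower scores, and the analysis seeks the best predictors. For association or prediction, a between-person marker is a legitimate result. This stands too, and it is why the person-mean term should be kept and reported. It does not rescue the single coefficient, which answers neither question cleanly and will be read against a mechanistic aim.

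**Centring is analysis-plan detail.** In part. But the article specifies fixed and random effects question by question, so the comment addresses a model that it states.

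**The split is no cure.** A reader might infer that the deviation term is free of all stable confounding. It is not if a trait alters recovery trajectories, and it does not address time-varying confounding or pain changing gait or fear. In a logistic mixed model, protection against constant-effect traits is approximate.

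**Conclusion.** The concern holds in a limited form. As stated, the model for research question four gives one blended coefficient per time-varying predictor, and a difference between patient types can appear as a predictor of pain. With no true effect, rejection was 12% to 63% across the assumed scenarios, against 1.5% to 7% for the within-person term when trait effects are constant. The lowest figure is only modestly above the 6% to 8% seen without confounding. The protocol gives no trait strengths or ICCs, so the direction and mechanism are firm and the size is illustrative.

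Two stronger conclusions are not supported. The documents do not show that any particular predictor will be confounded, or that a between-person association would be a false result. Nor do they justify resting every longitudinal claim on the deviation term alone, given its loss of power with about 30 people. The split is a cheap improvement to a stated model.

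**What to change.** In research question four, and for pain in research question three, enter each selected time-varying predictor as two terms: the person's mean over visits and the visit's deviation from that mean. Report both.

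- Interpret the deviation term as the within-person association, protected from time-constant traits with constant effects. State that it is not protected from traits that alter trajectories, from time-varying confounding or from reverse causation.
- Interpret the person-mean term, which bears on the between-person part of hypothesis 4, as an association open to confounding by patient type.
- Describe a predictor as tracking LBP within a person only when the deviation term supports it.

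Cost: re-coding of variables already collected, one extra parameter per predictor, and clearly lower power for the deviation term (roughly half that of the blended estimate at assumed ICCs of 0.6 to 0.7). A deviation term that is not significant should therefore be reported with its interval and not read as absence of a within-person relation.
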